## Abstract

**Background:**

Many older people with neuropsychiatric disorders such as Alzheimer's disease and frontotemporal dementia suffer from sleeping problems and often show nocturnal restlessness. Professionals and informal carers face considerable problems in solving these problems. Attempts to diminish these problems with medication in a safe and responsible manner have proven hardly effective or not effective at all. Therefore, nowadays the focus lies more on non-pharmacological solutions, for example by influencing environmental factors. There are indications that treatment with low-frequency acoustic vibrations, that is Physio Acoustic Sound (PAS) therapy, has a positive effect on sleeping problems. Therefore we study the effectiveness of PAS therapy in demented patients with nocturnal restlessness.

**Methods:**

In a randomized clinical trial, 66 nursing home patients will be divided into two groups: an intervention group and a control group. For both groups nocturnal restlessness will be measured with actiwatches during a period of six weeks. In addition, a sleep diary will be filled in.

For the intervention group the baseline will be assessed, in the first two weeks, reflecting the existing situation regarding nocturnal restlessness. In the next two weeks, this group will sleep on a bed identical to their own, but with a mattress containing an in-built PAS device. As soon as the patient is lying in bed, the computer programme inducing the vibrations will be switched on for the duration of 30 min. In the last two weeks, the wash-out period, the measurements of the intervention group are continued, without the PAS intervention.

During the total study period, other relevant data of all the implied patients will be recorded systematically and continuously, for example patient characteristics (data from patient files), the type and seriousness of the dementia, occurrence of neuropsychiatric symptoms during the research period, and the occurrence of intermittent co-morbidity.

**Discussion:**

If PAS therapy turns out to be effective, it can be of added value to the treatment of nocturnal restlessness in demented patients. Non-pharmacological PAS therapy is not only safe and patient-friendly, but it can also be widely used in a simple and relatively inexpensive way, both in institutions such as nursing homes and residential homes for the elderly, and at home. Ultimately, this may lead to a decrease in the frequent and still common use of psychotropic drugs. In addition, care needs of demented patients also may decrease as well as the number of preventable admissions to care institutions.

**Trial registration:**

Netherlands Trial Register (NTR): NTR3242

## Background

Many older people with neuropsychiatric disorders such as Alzheimer's disease [1] and frontotemporal dementia [2] often suffer from sleeping problems, especially nocturnal restlessness. The concept of nocturnal restlessness can be described as a disturbance of the normal sleeping pattern, manifesting itself in a certain way of motor and/or verbal behavior. In general, nocturnal restlessness should be placed in a wider context of behavioral disorders, that are often associated with dementia [3]. Common types of nocturnal restlessness include a change or even a reversal of the day/night rhythm, high motor activity levels during sleep, a frequent alteration of sleeping phases and a frequent crying out and/or wandering during the night. This disturbance of normal sleep may lead to or coincide with serious inconvenience and stress, not only for the patients themselves but also for their informal carers, which is an especially important reason to transfer (or admit early) a patient to a nursing home [4].

### Treatment of sleep disturbances in dementia

Nocturnal restlessness as well as other behavioral problems associated with dementia, are still mostly being treated with psychotropic medication such as hypnotics and antipsychotics in nursing homes as well as at home. The results of such treatments are often disappointing and negative side effects occur frequently. Research conducted in nursing homes has even demonstrated that this pharmacological approach has more adverse than positive effects [5,6].

Adequate control of the day/night rhythm by influencing lifestyle and environmental factors may sometimes lead to better results [4-10]. This finding stimulates further research on other, preferably non-pharmacological treatment options for the problems of nocturnal restlessness in dementia.

### Effectiveness of Physio Acoustic Sound therapy

A new non-pharmacological treatment option was found by chance by the staff of Zandhove, the central nursing home of Zorgspectrum Het Zand in Zwolle, the Netherlands. It arose from the successful therapeutic application of acoustic vibrations in order to reduce pain. This Physio Acoustic Sound (PAS) therapy was originally developed in Finland, where it has been used successfully for several decades, especially in patients with pain, stress, and rigidity.

The therapy is based on practical experience as well as research, both illustrating that low-frequency acoustic vibrations (27-113 Hz) can have positive effects on several symptoms. For instance, in an intervention period of five weeks, PAS therapy has led to a decrease in self-wounding, stereotype, and aggressive self-destructive behavior in patients with autism and development disorders [11]. Furthermore, a PAS therapy programme for the elderly has proven to improve their general wellbeing and functional capacity: bone formation and mobility improved, cholesterol levels were lower, and blood circulation was stimulated [12]. In another study, PAS therapy caused patients to be more relaxed with reduction of their pain symptoms [13,14]. The therapy also has shown positive short-term effects on motor symptoms in patients with Parkinson's disease, for example a decrease in rigidity, bradykinesia, tremor, and an increase in step length [15].

Of the many observed effects of PAS therapy, the following have now been officially recognized by the American Food and Drug Administration (Device Classification Name: vibrator, therapeutic; 510(k) nr. K934886, reg. nr. 890.5975; d.d. 06-09-1994): relaxation, reducing pain, and stimulating blood circulation.

Most of the results of PAS therapy have been obtained by treatment in a so-called PAS therapy chair. The chair contains acoustic equipment that generates a limited range of low-frequency vibrations (27-113 Hz). Controlled by computer programmes, these vibrations are led through the chair in a wave sequence. The chairs are now available in several countries, including the Netherlands, and are used for several treatment purposes [16].

### PAS therapy in sleep disturbances in dementia

Many of the effects of PAS therapy mentioned above have also been observed in daily practice in the nursing home Zandhove of Zorgspectrum Het Zand. Moreover, patients indicated that they were sleeping better after treatment in the PAS therapy chair. To investigate whether this particular effect also applies to demented elderly people, for whom nocturnal restlessness is a common cause of sleeping disorders, the same technique as in the chair was recently built-in in mattresses. These mattresses can be used on a standard high-dependency bed as used in most long-term care settings (Figure 1).

**Figure 1 F1:**
[figure not shown]
**High-dependency bed with PAS mattress and night table with computer which is normally locked up in the night table**.

## Methods and design

### General objective

The aim of this study is to test, by means of a randomized controlled trial, the hypothesis that application of PAS therapy with low-frequency acoustic vibrations to demented patients in nursing homes will lead to a significant decrease of nocturnal restlessness.

### Participants

The research population consists of demented nursing home patients residing in one of the five psychogeriatric nursing wards of Zorgspectrum Het Zand. Each ward has about 30 patients, who each have a single bedroom and share a common living room (8 to 10 people).

### Inclusion and exclusion criteria

Patients are included when diagnosed with the DSM-IV definition of dementia and who have been residing in the nursing home for a minimum of two months. Exclusion criteria are (1) the presence of (high risk of) a pressure sore, that is an indication for the preventive use of a different mattress, for example an alternative mattress to prevent pressure ulcers; (2) acute illness, for example pneumonia, exacerbation of heart failure, a recent stroke, and so on; and (3) a pacemaker, which could possibly interfere with the PAS instruments.

### Interventions

Patients will be randomized over an intervention group and a control group. The patients in the control group will sleep on their own high-dependency bed during the three periods of two weeks each. The patients in the intervention group will sleep, after the initial baseline period of two weeks, on a high dependency bed identical to their own for the second period of two weeks. The mattress of this bed, however, contains the same technique as the PAS therapy chair and will be controlled by an external computer. As the intervention can be controlled perfectly and safely via the computer regarding frequency, duration and intensity, the technique is considered suitable for this research. In the third and last (wash-out) period of two weeks they sleep again in their own bed.

The computer programme controlling the acoustic vibrations of the mattress will be switched on daily by the nursing staff during a period of two weeks. This will be done as soon as the patient is lying in bed. The programme will switch off automatically after 30 min. So as to not contaminate the results by the presence of the staff, the staff member will leave the patient's bedroom as soon as the mattress is switched on. The frequencies used in the programme lie between 27 and 40 Hz and will vary every two or three minutes.

These frequency settings of the intervention have been chosen after advice from Finnish professionals who have many years of experience with this intervention. The design of the programme used in this intervention was originally aimed at reducing pain, and the varying frequencies were based on Melzak and Wall's gate control theory [17].

The other therapeutic applications of PAS therapy described above, whose effectiveness has already been proven, are all based on this design as well.

### Sample size

In this study, it is assumed that the nocturnal restlessness in patients in the control group will remain stable, with a frequency of 80% episodes of nocturnal restlessness [18]. By applying PAS therapy, a conservative decrease of nocturnal restlessness of 30% is expected, resulting in a restlessness frequency of 50%. Taking into account a probability value of 5% (alpha), a power of 80% (1-beta), and a drop-out rate of 10%, 66 patients are needed in total, that is 33 in the intervention group and 33 in the control group.

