### Data collection

First, the following patient characteristics will be collected for both groups: age, gender, type of dementia, co-morbidity (by means of CIRS [20]), incontinence Yes or No, the use of restraints (for example fixation belts), medication (including psychopharmacological drugs), and other therapies.

In addition, the Bedford Alzheimer Nursing Severity Scale (BANS-S) [21] will be applied by the psychologist together with the nursing staff to get an impression of the severity of dementia. This validated scale contains seven items to assess functional and cognitive capacities as well as pathological symptoms. These items, scaled 1 to 4, are summed. The overall score ranges from 7 (no impairment) to 28 (complete impairment).

Although the traditional 'gold standard' assessing the quality of the sleep is polysomnography (PSG), it is difficult to apply PSG to patients with a moderate to serious form of dementia [22,23]. Therefore, in studies like this, often more feasible assessment methods are used, like observation-oriented techniques and actigraphy. Actigraphy is a less invasive method than PSG, offering a reliable way to estimate sleep/wake parameters including nocturnal restlessness [24]. In this study we will use both actigraphy and sleep diaries.

The nocturnal restlessness will be measured by validated actigraphy [25-27] in the intervention group as well as in the control group on the basis of the following sleep/wake parameters [28,29]: (1) nocturnal restlessness: average motor activity during the night; (2) sleep efficiency: the number of hours the patient is lying in bed and actually sleeping; (3) wake bouts: the number of episodes the patient is awake during the night; (4) inter-daily stability: the degree of stability in activity patterns over longer periods of time; (5) intra-daily variability: the degree of inconstancy in rest and activity during a day [28,29].

When considering nocturnal restlessness it is important to take measurements during a period of at least two weeks. In this way, the statistic power will increase [30].

To determine the degree to which the actimeters respond to the acoustic vibrations of the mattress themselves, a control actimeter is placed on the mattress in advance.

In addition, other relevant sleep observation data of every patient will be written down in a sleep diary, in which nocturnal restlessness and the day/night rhythm, as observed by the nursing staff will be recorded.

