### Statistical analysis

In order to process the data to test our hypothesis, the statistical software programme SPSS-19 [34] will be used. First, data will be checked for missing values and normal distribution. It will be examined whether there is a significant difference in both nocturnal restlessness and degree of neuropsychiatric symptoms between the intervention group and the control group.

To analyze the actigraphy variables and the variables measured by means of NPI-NH (T0, T1, and T2) integrally, a multilevel regression model (Mixed Models) will be used. In this study, the Basic Two-Level Regression Model [35] will be used, in which the actigraphy variables and NPI-NH variables are the lowest levels (that is dependent variable) and the research participants the highest level (independent variable).

The multilevel analysis enables us to calculate the degree of nocturnal restlessness and neuropsychiatric symptoms despite the unequal number of observations per individual (missing values/dropouts). This means that all data will be included in the analysis, including the data of participants who will meet stop criteria during the investigation and for whom the study has to be terminated early.

If there is interaction effect between time and group, a post-hoc analysis will be performed, taking into account that T0-T1 indicates PAS therapy effects and that T1-T2 indicates the long-term effects of PAS therapy. The analyses will be corrected for basic differences in the characteristics of the patients belonging to the intervention group and the control group respectively. The data in the sleep diaries will first be coded and later analyzed separately by means of describing statistics.

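### The 66-patient calculation reproduces only with an undeclared one-sided 5% test, and it is for a restlessness proportion that no stated analysis tests

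*Protocol article*

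**What the plan says.** All references are to the protocol article.

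- **Sample size.** Restlessness in the control arm is taken to stay at 80%. For the intervention arm, "a conservative decrease of nocturnal restlessness of 30% is expected, resulting in a restlessness frequency of 50"%. The section then states: "Taking into account a probability value of 5% (alpha), a power of 80% (1-beta), and a drop-out rate of 10%, 66 patients are needed", split 33 and 33. It names neither the test nor its sidedness; the level is given only as "a probability value of 5% (alpha").
- **General objective.** The hypothesis is directional: the therapy "will lead to a significant decrease of nocturnal restlessness".
- **Statistical analysis.** The wording is non-directional: "It will be examined whether there is a significant difference in both nocturnal restlessness and degree of neuropsychiatric symptoms" between the two groups. Actigraphy and NPI-NH variables at T0, T1 and T2 go into a two-level mixed model. The sleep diary is coded and then summarised descriptively.
- **Data collection.** Five actigraphy parameters are listed, the first being "nocturnal restlessness: average motor activity during the night".
- **Primary outcome measures.** The actigraphy parameters and the staff-completed diary are both primary. No rule is given for classing a patient or a night as restless or not.

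**The concern.** There are two separate difficulties.

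First, a 5% alpha given without a side, in a plan that looks for a difference between groups, is ordinarily read as two-sided. On that reading 66 patients are too few for the section's own inputs.

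Second, whatever the sidedness, the inputs are two frequencies, whereas the outcome tested is a set of actigraphy measures led by a continuous average. The power claim belongs to a comparison that the analysis section does not contain.

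What is at stake is how the result is read. A null finding would be taken to come from a trial with 80% power. If a one-sided 5% test was meant, readers need to know that too, because it allows twice the usual false-positive probability in the favourable direction.

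**Working it through.** **Inputs (Sample size section).** p1 = 0.80, p2 = 0.50, difference 0.30, mean 0.65, alpha 0.05, power 0.80, drop-out 10%, allocation 1:1. Normal quantiles: 1.645 (one-sided 5%), 1.960 (two-sided 5%), 0.842 (80% power).

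**Formulas for evaluable n per arm.**

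- Unpooled: n = (z_alpha + z_beta)² × [p1(1−p1) + p2(1−p2)] / 0.30², where the bracket is 0.16 + 0.25 = 0.41.
- Pooled: n = [z_alpha × √(2 × 0.65 × 0.35) + z_beta × √0.41]² / 0.30², with √0.455 = 0.6745 and √0.41 = 0.6403.
- Arcsine: n = 2(z_alpha + z_beta)² / h², with h = 2·asin√0.80 − 2·asin√0.50 = 0.6435.

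**Reproducing the plan's figure (one-sided 5%).**

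- Unpooled: 28.2, so 29. 29/0.9 = 32.2, so 33 per arm and **66** in total.
- Arcsine: 29.9, so 30. 30 × 1.1 = 33 per arm and **66** in total. (30/0.9 gives 34 per arm, 68 in total.)
- Pooled: 30.2, so 31, then 35 per arm and 70 in total: close, but not a match.

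**Same inputs, two-sided 5%.**

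| Formula | Evaluable per arm | After 10% drop-out, per arm | Total |
|---|---|---|---|
| Unpooled | 35.8, so 36 | 40 | 80 |
| Arcsine | 37.9, so 38 | 42–43 | 84–86 |
| Pooled | 38.5, so 39 | 43–44 | 86–88 |

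Where a range is shown, the lower value multiplies by 1.1 and the higher divides by 0.9. A continuity correction raises the pooled figure to 45 evaluable per arm, or 100 in total. No two-sided variant comes near 66.

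**Two-sided power with 66 randomised.** Evaluable per arm: 33 × 0.9 = 29.7, taken as 30.

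- Pooled: (0.30 × √30 − 1.960 × 0.6745) / 0.6403 = 0.50, so power is **69%**. Exact enumeration of the chi-square test also gives 69%.
- Unpooled: 0.30 × √30 / 0.6403 − 1.960 = 0.61, so power is **73%**.
- With no drop-out at all (33 per arm): 73% pooled, 77% unpooled.

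For comparison, one-sided 5% with 30 per arm gives 80% (pooled).

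**Match between calculation and analysis.** The calculation uses a frequency of restlessness. The mixed model takes the actigraphy and NPI-NH variables as dependent variables. The diary, the other place where a frequency might arise, is not tested. No SD, within-patient correlation or target difference is given for any actigraphy variable, so power for the planned model cannot be derived.

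**What can be said on a continuous scale.** With 30 evaluable per arm, a two-sided 5% t-test has 80% power for a difference of 0.74 SD. If the analysis adjusts for the T0 value, this shrinks by √(1 − ρ²), where ρ is the T0–T1 correlation. The documents do not give ρ. For assumed values of 0.5 and 0.8 the detectable difference is 0.64 and 0.44 SD. These figures are for a simple T1 comparison and only indicate the order of size for the planned T0–T1–T2 model.

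**The case against.** The strongest reply is that the sum is not wrong. The objective speaks of a decrease, a one-sided test fits that, and 66 then follows exactly. This stands in part: the defect is undeclared sidedness in tension with the analysis section, not a demonstrable slip in arithmetic. But a directional hypothesis does not declare a one-sided test, and no section does.

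The reply also checks three stronger readings that a reader might infer.

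- *The trial has 69% power, so it is underpowered.* The documents do not support this. The 69–73% applies only to a two-sided comparison of proportions. As an illustration, suppose that 80% and 50% were the shares above a cut-off on a normal scale with equal SDs. The shift would be 0.84 SD, and a two-sided t-test with 30 per arm would have about 89% power. That is an assumption, not a fact from the plan, but it shows that power for the actigraphy analysis could lie above 80% as well as below.
- *The sized outcome is never analysed.* This is too strong. Whether the assumed frequency is per patient, per night or per episode is left open, the diary is described, and the number of wake bouts is among the actigraphy variables. What the text supports is that no test of a restlessness proportion is stated.
- *The 30% might be a relative fall.* The same sentence fixes the resulting rate at 50%, so it means 30 percentage points. Whether that is conservative depends on evidence not shown.

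**Conclusion.** The point holds in two parts.

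1. The stated 66 patients and 80% power agree only under a one-sided 5% test that the article does not declare. At two-sided 5% the same assumptions require 80 to 88 patients by the usual formulas, and 66 give about 69% (pooled) to 73% (unpooled) power with 30 evaluable per arm. This rests on reading the calculation as a comparison of two independent proportions, one observation per patient. The section does not name its method, but that reading reproduces its figure.
2. Whichever sidedness was meant, 80% power is not supported for the outcome that is tested. Its actual power is unknown from the document and may be higher or lower.

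This is not something an article simply leaves to a fuller document. The calculation, the outcomes and the analysis are all printed, and they do not fit together.

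**What to change.** Keep 66 patients and revise the wording:

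- State whether the test is one-sided or two-sided, and make General objective, Sample size and Statistical analysis agree.
- If two-sided, restate the power for 80% v 50% as about 69–73% with about 30 evaluable per arm, labelled as applying to that comparison of proportions only. If one-sided 5% was intended, say so and give the reason.
- Name one primary actigraphy variable and one contrast from the planned T0–T1–T2 mixed model.
- For that variable, state the difference detectable with about 30 evaluable per arm: about 0.74 SD at 80% power, two-sided, without baseline adjustment. If a smaller adjusted figure is quoted, give the assumed within-patient correlation and a range for it.
- Optionally, write 30 percentage points in place of 30%.

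The cost is wording and a short calculation. No extra patients are needed. If the test is two-sided, the power stated for 80% v 50% becomes less favourable.

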### Randomization

By means of blinded block randomization with group sizes of six, the randomization scheme will determine which patients will be placed in the intervention group and the control group. The intervention is not blinded because it is visible for the caregiver (box with computer below the bed and faintly audible (a very low buzz).

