### Procedure

After including the patients for participation in the study, they will be divided into an intervention and control group by means of randomization. We have not opted for a crossover design, as it cannot be estimated how long the wash-out period will be [19]. For the sake of the validity of the results to be obtained, a period of six weeks (2 + 2 + 2) has been chosen for the intervention group as well as for the control group. During this total period, both groups of demented patients will continuously wear an actiwatch (respironics type AW2) on the non-dominant wrist. Practice has shown that this watch hardly causes any nuisance or no nuisance at all.

In addition, a daily sleep diary will be kept by the nursing staff for all participants.

In the first two weeks, the baseline situation (T0) of the intervention group and control group will be measured by means of the actiwatch. In the next two weeks, as the intervention is executed in the intervention group, in both groups the actiwatch measurements will be continued (T1). In the last two weeks the wash-out of the intervention will be measured and again in both groups the actiwatch measurements will be continued (T2).

During the whole period, the doors of the bedrooms of all participants in both groups will remain closed during the night, in order to prevent disruptions. Yet, if a patient or staff member enters/leaves the room, this will be noted in the sleep diary.

After the study period of six weeks, the actiwatches will be read out. The collected data per patient will be recorded, together with the other relevant data. These include registered changes in the situation of the patients during the study period, for example (1) possible additional co-morbid illness(es) that may lead to a change in the level of motor restlessness or in the normal day/night pattern of the patient (for example pneumonia, delirium, urinary retention, constipation), or (2) changes in the use of psychotropic drugs, therapies, and/or use of restraints.

A schematic representation of the procedure can be found in Table 1.

**Table 1 T1:** Measurements overview

Moment	T0	Baseline	T1	Baseline	T2	Intervention	T3	Intervention	T4	Wash-out	T5	Wash-out	T6
Week	0	1		2		3		4		5		6	
Actiwatch		Continuous		Continuous	*Charging*	Continuous		Continuous	*Charging*	Continuous		Continuous	
NPI-Q					T2				T4				T6
BANS-S	T0												
Patient characteristics	T0												

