## Trial status

The study started recruiting participants in July 2011. This is still ongoing. Soon after the first recruitments, the interventions and the measurements started as well. We expect the results to be published at the end of 2013.

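### A single block size of six, published during recruitment to an open trial in one organisation, makes up to a quarter of allocations certain in advance to a fully informed observer

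*Protocol article*

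**What the plan says.** The Randomization section of the protocol article assigns patients "By means of blinded block randomization with group sizes of six". It names one size and no variation. The next sentence states: "The intervention is not blinded because it is visible for the caregiver".

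Other sections describe the setting:

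- Sample size: "66 patients are needed in total, that is 33 in the intervention group and 33 in the control group", so allocation is 1:1.
- Participants: all patients are "residing in one of the five psychogeriatric nursing wards of Zorgspectrum Het Zand".
- Procedure: "After including the patients for participation in the study, they will be divided into an intervention and control group by means of randomization".
- Interventions: "The patients in the intervention group will sleep, after the initial baseline period of two weeks, on a high dependency bed identical to their own". Until then both arms sleep in their own beds.
- Trial status: "The study started recruiting participants in July 2011. This is still ongoing".

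**The concern.** In the Randomization section, blinded most plausibly means that the list is hidden. A hidden list protects the next allocation only if that allocation cannot be worked out from what is already known. With one fixed and published block size, and arms that become visible in use, the end of a block can be worked out without seeing the list: once three patients of a block are in one arm, the rest of that block must go to the other.

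Randomising after inclusion does not remove this. What matters is whether the next arm can be foreseen when someone decides whom to include, and when. Entry leaves room for judgement (for example, a high risk of a pressure sore, or acute illness), and consent comes through representatives, so timing could shift. If it did, the arms could differ in ways that the planned correction for recorded patient characteristics would not fully remove. With 33 per arm, a few steered enrolments could matter.

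**Working it through.** **Inputs.** Block size 6 (Randomization); 1:1 allocation and 66 patients (Sample size); PAS bed in place only after a two-week baseline (Interventions). The article gives no predictability figure to reproduce. Its numbers fit together: 66/6 = 11 whole blocks, and 11 × 3 = 33 per arm.

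**Assumptions for the upper bound.** One unstratified list, patients randomised one at a time, and an observer who knows the block start and every earlier allocation in the block.

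**Certain allocations.** A 3 + 3 block has C(6,3) = 20 equally likely sequences. An allocation is certain once one arm has its three patients.

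- 4th: the first three are alike in 2 of 20 sequences, 0.10.
- 5th: the first four split 3:1 in 2 × C(4,3) = 8 of 20, 0.40.
- 6th: always, 1.00.

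The sum is 1.5 per block, and 1.5/6 = 25%. Over 11 blocks this is 16.5 of 66. The closed form 1/(m + 1), with m = 3 per arm, also gives 25%.

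**Best guess.** Guess the arm with fewer patients so far, and toss a coin when they are level. The chance of being right at positions 1 to 6 is 0.5, 0.6, 0.6, 0.7, 0.7 and 1.0. The sum is 4.1, and 4.1/6 = 68.3%, against 50% by chance.

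**If the latest allocations are not yet known.** Each unseen allocation moves the certainty probabilities one position later, and the last one drops off the end of the block.

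| Latest allocations unseen | Certain per block | Certain share | Best guess right |
|---|---|---|---|
| 0 | 0.10 + 0.40 + 1.00 = 1.5 | 25% | 68.3% |
| 1 | 0.10 + 0.40 = 0.5 | 8.3% | 60.0% |
| 2 | 0.10 | 1.7% | 56.7% |
| 3 | 0 | 0% | 53.3% |

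**Which row applies** depends on the pace of recruitment and on when staff learn the arm. The article gives neither. As an illustration, assume that the arm is first seen when the bed changes and that 66 patients are spread evenly from July 2011 to the end of 2013. That is the longest window Trial status allows, about 130 weeks, or one patient per two weeks. About one allocation is then typically unseen, giving roughly 8%. With random (Poisson) arrivals at the same rate, the weights for 0, 1 and 2 unseen are 0.368, 0.368 and 0.184, and 0.368 × 25% + 0.368 × 8.3% + 0.184 × 1.7% is about 13%. Faster recruitment lowers both figures.

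**Varying the size among 4, 6 and 8 (equally likely).**

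- Possible sizes and block boundaries known, but not the size of the current block: certainty arises only in blocks of eight, after one arm has reached four. That is 2m/(m + 1) = 8/5 = 1.6 allocations per block of eight. Three blocks, one of each size, hold 4 + 6 + 8 = 18 patients, so the share is 1.6/18 = 8.9%, about 9%. Simulation gave the same.
- Possible sizes known, boundaries unknown: simulation of 1,500 sequences of 66 gave 2.5% certain and 67.8% of best guesses right.

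**The case against.** The strongest objection is that the 25% describes an observer whom the protocol may never produce. The box and the buzz that reveal the arm do not exist until week 3, so recent allocations need not be known when the next patient is included. Patients have single rooms spread over five wards. The Procedure wording also fits randomisation in batches, and if whole batches of six were included first, prediction would not matter. The list is described as blinded, and inclusion precedes randomisation.

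Most of this stands, and it limits the size of the point. A reader might infer that a quarter of allocations simply are predictable, or that every earlier arm can be seen on the ward. The documents do not support that, given the two-week baseline. Nor do they show that staff stay unaware of the arm until the bed changes.

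A reader might also infer that the nursing staff who keep the sleep diary are the people who enrol. No section says so. Diary scoring by unblinded staff is a separate question that block size does not affect. Who holds the list, and whether an allocation is released only after registration, are details that an article leaves to the full protocol, so their absence is not part of this point.

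The objection does not remove the stated design choice. The size is fixed, it was published during recruitment, and the intervention is open. Hiding the list does not cancel that combination.

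**Conclusion.** The point holds as a limited weakness in a stated design choice. Up to 25% of allocations on average, about 16 of 66, are certain in advance to someone who knows the block start and all earlier allocations on a single 1:1 list, and such a person's best guess is right 68.3% of the time. These are upper bounds. They fall to 8.3%, 1.7% or 0% certain when the latest one, two or three allocations are unseen, and they assume no stratification and one-at-a-time randomisation, which the article does not settle. Selection bias at enrolment is possible. Nothing in the document shows that it occurred or that anyone was placed to cause it.

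**What to change.** For patients still to be enrolled, draw a new list with randomly varying block sizes, for example 4, 6 and 8, and do not disclose the sizes to those who enrol. This cuts the certain share from 25% to about 2.5% if block boundaries are unknown, or about 9% if they are known. A fully informed guesser would still be right about 68% of the time, so the benefit is mainly that certain knowledge of the next arm is removed.

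The cost is one new list and possibly a small imbalance. If the current block of six is completed before the switch, the worst case at 66 patients is a final block of eight cut off after four patients in the same arm, a difference of four (35 and 31 instead of 33 and 33). Allocations already made cannot be changed by this.
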